## Abstract

**Background:**

Though behavioral activation (BA) has been shown to be effective for depression, evidence in patients with advanced cancer has not been established. This study aimed to examine the effectiveness of a BA program on depression in this population.

**Methods:**

A randomized controlled trial with a wait-list control group (waiting group) of 38 patients with advanced cancer and depression will be conducted at three sites in Japan. The BA program consists of seven sessions. Outcome measures will be evaluated at three times in the intervention group; at the entry, at the end of the intervention and 4 months after the end of the intervention and four times in the waiting group: at the entry, before the intervention, at the end of the intervention, and 4 months after the end of the intervention. Primary outcome is Beck Depression Inventory-II (BDI-II) score. To examine the main effect of the intervention, two-way repeated measures analysis of variance (ANOVA) will be conducted, with timing and intervention status as the independent variables and BDI-II score as the dependent variable. One-way repeated measures ANOVA will be conducted to combine data from the intervention and control groups and examine changes in BDI-II scores by timing in both groups. Secondary endpoints (anxiety, quality of life, spirituality, degree of behavioral activation, value, and pain) will be evaluated with rating scales. Two-way repeated measures ANOVA will be conducted to examine whether there are differences between the groups before and after the intervention, with timing and intervention status as the independent variables and scores on each rating scale as the dependent variables.

**Discussion:**

This multicenter randomized controlled trial is the first study to assess the effectiveness of BA on depression in patients with advanced cancer. Our findings will provide evidence about the effectiveness of BA on depression and provide an intervention option that is acceptable and feasible for the treatment of depression in this population. The results of this study will lead to improved mood and rebuilding to regain life purpose and value in this vulnerable population.

**Trial Registration Number:**

jRCT, jRCT1030210687, Registered 22 March 2022, https://jrct.niph.go.jp/en-latest-detail/jRCT1030210687.

**Supplementary Information:**

The online version contains supplementary material available at 10.1186/s12885-023-10926-y.

## Background

Patients with advanced cancer have unmet needs in the financial, health system, health information, psychological, physical, and daily living domains. These unmet needs are associated with distress, depression, and anxiety in patients with advanced cancer [1]. They also experience existential distress as a result of a shortened lifespan, prognostic uncertainty, altered interpersonal relationships, and impaired physical functioning, sense of autonomy, and personal control [2]. Previous studies have reported that psychological distress, particularly depression, is frequently observed in patients with cancer, especially advanced cancer [3–6].

Depression in patients with advanced cancer leads to adverse effects such as impaired quality of life (QOL) [7], risk of suicide [8], and psychological burden on their family [9, 10]. Therefore, an important challenge in clinical oncology is determining which interventions are most acceptable and feasible to treat depression in patients with advanced cancer [11].

There is a general preference for psychotherapy in the most common psychiatric disorders, but also specifically for patients with cancer [12, 13]. Meaning-based individual psychoeducational interventions [14] and legacy-based interventions have been found to be beneficial for individuals near the end of life [15]. However, there are few brief evidence-based psychotherapies that are simple to deliver and integrated with cancer care from the time of diagnosis to advanced disease [16, 17]. Previous studies have not shown consistent results regarding effectiveness; many methodological problems have been pointed out [11].

Patients living with advanced cancer experience various types of psychological and social distress such as anxiety about worsening disease, fear of death, and hopelessness about life, which often lead to mental health problems such as depression and high risk of suicide [18]. Quite a few patients with cancer are reluctant to directly face their concerns regarding death, symptom burden, loss of control, and other factors because their experiences are psychologically traumatic [19]. Several studies have shown the effectiveness of cognitive restructuring-based cognitive behavioral therapy (CBT) for depression or anxiety in patients with advanced cancer [20, 21], while other studies have reported no effectiveness [22]. Evidence about the effectiveness of CBT in patients with advanced cancer is inconsistent.

Behavioral activation (BA), developed as a psychotherapy for depression, aims to improve mood and rebuild life to regain purpose and value through the reuse of the patient’s inherently healthy aspects as well as human and social resources, rather than addressing the pathology of depression and negative thoughts and feelings, which had been the focus of previous psychotherapies. Many studies have demonstrated the effectiveness of BA in depression with a high level of evidence [23]. Some studies have evaluated the use of BA in patients with breast cancer or cancer-free survivors [24, 25]. However, no studies have explored the effectiveness of BA in patients with advanced cancer.

To explore the applicability of BA to patients with cancer, we have developed a BA program for patients with cancer and tested the preliminary effectiveness in a pre-post study without a control group [26]. This program was designed to (1) understand confining life patterns through activity records, (2) discuss specific activity plans and devise ways to implement them, (3) focus on positive aspects such as the joy and sense of accomplishment associated with activities, (4) clarify what is important to the patient as well as the joy and value of life, (5) break free from pathological anxiety and worry, and (6) create a life plan for the future. The program consists of seven sessions. The preliminary study showed high rates of treatment completion and remission of depressive symptoms, regardless of the stage of cancer, suggesting that BA could be a potentially effective psychological intervention for patients with advanced cancer [26].

This multicenter randomized controlled trial aims to examine the effectiveness of a BA program on depression in patients with advanced cancer compared to a wait-list control group (waiting group).

## Methods

### Study setting

Participants will be recruited from May 2022 to March 2024 by the Department of Psycho-Oncology at the National Cancer Center Hospital, the Department of Psycho-Oncology at the National Cancer Center Hospital East, and the Department of Psychiatry at Tohoku University Hospital, Japan.

### Patient and public involvement

Based on feedback from patients who participated in the pilot study that the program contents were very useful but that shorter sessions would be more accessible [19], this BA program [26] was modified to include seven instead of eight sessions. Patients or the public will not be involved in the design, reporting, or dissemination plans of this study.

### Eligibility

#### Inclusion criteria

All study participants will meet the following criteria: (1) diagnosis of cancer or recurrence for more than 1 month with clinical stage III or IV disease for which the attending physician has determined that radical cure is not a goal, based on confirmation from the medical record or the attending physician directly; (2) expected prognosis of approximately 1 year or more according to the attending physician; (3) ability to participate in all sessions; (4) depression, defined as 16 ≥ points on the Beck Depression Inventory-II (BDI-II) (regardless of whether or not they meet the diagnostic criteria for depression); (5) age of 20–64 years, or age of ≥ 65 years with ≥ 24 points on the Mini Mental State Examination-Japanese (MMSE-J) ; (6) Eastern Cooperative Oncology Group (ECOG) performance status (PS) of 0 or 1 according to the attending physician; (7) ability to speak Japanese; and (8) written informed consent to participate in this study and wish to continue with the intervention.

#### Exclusion criteria

The exclusion criteria will be as follows: (1) severe physical or psychological symptoms (cognitive dysfunction [defined as a score of ≤ 23 on the MMSE-J performed for all prospective participants aged ≥ 65 years or those aged 20–64 years who did not seem to understand routine instructions during the preliminary interview], impaired consciousness, severe depression with psychotic symptoms, imminent suicidal ideation, and history of suicide attempt); (2) receipt of psychological intervention, such as BA, by mental health professionals before enrollment; (3) use or planned use of any psychotropic drug during the program, except for temporary emergency use after enrollment based on the discretion of the attending physician; (4) substance dependence based on the diagnostic criteria in the Diagnostic and Statistical Manual of Mental Disorders, 5th edition; and (5) difficulty in participating in this program due to other reasons, according to the attending physician or researchers.

The waiting group will be informed that if the need for medication arises during the waiting period, they will be excluded from the study but can be offered another program equivalent to the BA program if they wish.

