#### Discontinuation criteria

The discontinuation criteria will be as follows: (1) serious adverse events or adverse reactions that make it difficult to continue the intervention; (2) worsening of physical or psychiatric symptoms, or emergence of new symptoms that make it impossible to continue the intervention; (3) patient desire to discontinue the intervention; (4) interval of 1 month or more between sessions attended; (5) regular use of psychotropic drugs at the discretion of the attending physician during the implementation of the program or while waiting; (6) meeting the exclusion criteria while waiting; and (7) any other reason for which the attending physician deems it necessary to discontinue the intervention.

If this study will be discontinued, the date on which the decision for discontinuation was made and the reason for discontinuation will be noted on the case registration form. The data center will be informed of the discontinuation.

If serious adverse events or adverse reactions, such as worsening of psychiatric or physical symptoms, occurs and it is deemed difficult to continue the intervention, the therapist will promptly inform the research director at each research institution and discontinue this study. The research director at each research institution contacted will promptly inform the research representative and data center of the decision for discontinuation.

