#### Patient disadvantages and how to minimize them

Since this is a study examining the effects of BA, a behavior-focused psychotherapy, on depression in patients with advanced cancer, we believe that the physical and psychological disadvantages to the study participants will be minimal. However, we will give due consideration to their physical and psychological condition, bearing in mind that they might experience stress due to the content of the intervention program and questionnaires. If exclusion criteria are met during the waiting period, such as worsening of psychiatric symptoms, the patient’s participation will be stopped immediately, and appropriate medical treatment, such as a visit to the psychiatry department of each research facility, will be provided. In addition, patients with a BDI- II score of 21 (moderate) or higher will be enrolled if they wish to participate in the study after being fully informed that they might benefit from pharmacotherapy and the study will be terminated immediately and they will be switched to regular psychiatric care if they experience worsening of psychiatric symptoms based on the discontinuation criteria.

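### Rules triggered by psychiatric worsening or medication need end study participation with no stated further BDI-II collection, so T2 scores go missing for outcome-related reasons

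*Protocol article*

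**What the plan says.** Three sections of the protocol article describe what happens when a randomised patient deteriorates or needs psychotropic drugs.

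- **Exclusion criteria.** Waiting-group patients are told that "if the need for medication arises during the waiting period, they will be excluded from the study". They may then be offered a program equivalent to the BA program.
- **Patient disadvantages and how to minimize them.** If an exclusion criterion is met during the wait, with psychiatric worsening as the example, the patient's "participation will be stopped immediately". For patients entering with BDI-II of 21 or more, "the study will be terminated immediately and they will be switched to regular psychiatric care if they experience worsening of psychiatric symptoms".
- **Discontinuation criteria.** Criterion (5) is "regular use of psychotropic drugs at the discretion of the attending physician during the implementation of the program or while waiting". Criterion (6) is "meeting the exclusion criteria while waiting". For worsening or a serious event, the text reads: "it is deemed difficult to continue the intervention, the therapist will promptly inform the research director at each research institution and discontinue this study". What is recorded is that "the date on which the decision for discontinuation was made and the reason for discontinuation will be noted on the case registration form".

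Two other sections bear on the consequences. Study procedure keeps a registered patient in the database unless consent is withdrawn, sets 4 months between successive assessments, and allows questionnaires to be completed at home. Major statistical analysis places all randomised subjects in the primary analysis by intention to treat and names multiple imputation for missing data.

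**The concern.** T2 is the end of the program in the intervention group and the last assessment before the program in the waiting group. It is therefore the one follow-up at which treated and untreated patients are compared as randomised. Needing psychotropic medication and worsening psychiatrically are events after randomisation that are closely related to depression, which BDI-II measures. If they end participation in the study, and not merely the wait or the program, the T2 scores most likely to be lost are those of patients doing badly. With 38 patients in total, a few such losses matter, and a score not collected at T2 cannot be recovered at analysis.

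**Working it through.** **1. What the rules stop.** The Exclusion criteria sentence refers to the study, and the Patient disadvantages section refers to participation and to the study. Discontinuation criteria is less clear: several items, such as (1), (2), (3) and (7), concern continuing or stopping the intervention, while the reporting paragraph speaks of discontinuing the study. No section says that T2 to T4 questionnaires continue after a stop.

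**2. What is still available for a removed patient.** The registration, the T1 scores, and the date and reason for stopping remain. With T1 and T2 four months apart and no BDI-II between them, no observed score carries the deterioration. An imputation model built on T1 scores and on patients who stayed would tend to give removed patients milder T2 scores than they had.

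**3. Do the rules differ by arm before T2?**

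| Trigger | Waiting | Intervention |
|---|---|---|
| Need for medication (Exclusion criteria) | yes | no |
| Regular psychotropic use, criterion (5) | yes | yes |
| Meeting exclusion criteria, criterion (6) | yes | no, but (1), (2) and (7) are close counterparts |
| Gap between sessions, criterion (4) | no | yes, but not tied to depression |

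The clear difference is the threshold. The waiting group can be removed on need alone. Criterion (5) requires regular use, and exclusion criterion (3) tolerates temporary emergency use.

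**4. Illustration of size.** The plan gives no figure for such removals. Its nearest figure is the dropout allowance: 3/32 = 9.4%, rounded to 10%. That allowance is defined in Power and sample calculation in a way that appears to leave out patients who meet the exclusion criteria, so it supplies no usable count.

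Inputs from the article: 38 patients randomised 1:1, so 38/2 = 19 per arm; SD 7.84; target difference 3.5. Assumed, not from the article: the numbers removed (n) and the excess (e) of true over imputed T2 scores, taken as 5 to 10 points.

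Higher BDI-II is worse, so the benefit is the waiting mean minus the intervention mean. It is understated by

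(n_wait × e_wait − n_int × e_int) / 19.

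- One net removal in the waiting arm: 5/19 = 0.26 to 10/19 = 0.53 points.
- Two net removals in the waiting arm: 10/19 = 0.53 to 20/19 = 1.05 points understated.
- Two net removals in the intervention arm: the same amounts, overstated.
- Equal numbers and equal excess: 0.
- Two in each arm, excess 10 (waiting) and 5 (intervention): (20 − 10)/19 = 0.53 understated.

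For scale, the standard error of a raw T2 difference is 7.84 × √(2/19) = 2.54. Then 0.53/2.54 = 0.21 and 1.05/2.54 = 0.41. Against the target, 0.53/3.5 = 15% and 1.05/3.5 = 30%.

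**5. Does imputation from T1 remove the shift?** A simulation assumed removals only in the waiting arm (5 to 20% of it), a correlation of 0.5 between T1 and T2, and a correlation of 0.5 to 0.8 between removal tendency and T2 score. Single regression imputation from T1, standing in for multiple imputation, still left the waiting mean 0.3 to 1.8 points too low. This shows that imputation from T1 alone can leave a shift. It does not show that the trial will have one of that size or in that direction.

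**The case against.** The strongest reply is that nothing is contradicted. All randomised subjects are in the primary analysis, registrations are kept, and missing values are imputed, so a removed patient can still be analysed as randomised. That stands. A reader might infer that removed patients are dropped from the analysis and that the intention-to-treat claim is false; the article does not say so.

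A second reply is that the wording is loose. Taken literally, discontinuing or terminating the study would end the whole trial, which is plainly not meant, and follow-up after stopping may be set out in the full protocol. This carries weight for Discontinuation criteria. It carries less for the other two sections, whose wording plainly reaches the patient's participation. If the full protocol does continue assessment, the published wording, including what waiting patients are told, still needs correcting.

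Third, the difference between arms is partly nominal. That also stands. A reader might take "interval of 1 month or more between sessions attended" as outcome-related loss in the intervention arm, but a gap may simply reflect cancer treatment or physical illness. No BDI-II score itself triggers removal in either arm.

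Fourth, the unseen imputation model could use the recorded reason for stopping, and a sensitivity analysis could shift the imputed scores of removed patients. Either would help, but each replaces a score that could have been observed with an assumption.

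**Conclusion.** The point holds as one of avoidable informative missing data. Followed as written, the rules lose T2 BDI-II for reasons related to the primary outcome, partly under a medication threshold that applies only to the waiting group, and imputation from T1 is unlikely to repair this. Intention to treat is weakened, not breached.

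The direction and size of any bias cannot be determined from the documents. A reader might infer that the benefit will be understated because the waiting group has the stricter threshold. That would require more removals, or larger excess scores, in that group, and the article gives neither. The illustrated 0.53 to 1.05 points rests wholly on assumed counts and excess scores, and is below half of one standard error. The case for changing the text is that the loss is preventable at little cost.

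**What to change.** Keep every clinical stopping rule, but state that it stops only the wait or the program. Then:

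- Collect BDI-II at the scheduled times from every randomised patient in both arms unless consent is withdrawn. It is self-reported, and home completion is already allowed.
- Analyse patients as randomised, and record the start of psychotropic medication or of the substitute program as intercurrent events.
- Reword the waiting-group sentence in Exclusion criteria to match the regular-use threshold of discontinuation criterion (5), and change the patient information accordingly.

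The cost is revised wording and a few extra questionnaires. Some T2 scores will reflect medication or the substitute program and may dilute the contrast with waiting. A sensitivity analysis can set those scores aside, which is possible only if the wider collection has been made.

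### The medication and worsening triggers for taking a patient off study are inconsistent and, as written, easier to meet in the waiting group during T1–T2

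*Protocol article*

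**What the plan says.** All references are to the protocol article.

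**Medication**
- Exclusion criteria, item 3, bars "use or planned use of any psychotropic drug during the program, except for temporary emergency use after enrollment".
- The last paragraph of Exclusion criteria is addressed to the waiting group only. It says: "if the need for medication arises during the waiting period, they will be excluded from the study but can be offered another program equivalent" (meaning BA-equivalent). The offer is for those who wish it.
- Discontinuation criteria, item 5, stops a patient for "regular use of psychotropic drugs at the discretion of the attending physician during the implementation of the program or while waiting".

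**Meeting exclusion criteria after entry**
- Discontinuation criteria, item 6, is "meeting the exclusion criteria while waiting". No matching item exists for patients on the program.

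**Worsening**
- Discontinuation criteria, item 2, is "worsening of physical or psychiatric symptoms, or emergence of new symptoms that make it impossible to continue the intervention".
- The closing paragraph of the same section acts on worsening once continuing is judged difficult, which is a lower bar.
- Patient disadvantages and how to minimize them states: "If exclusion criteria are met during the waiting period, such as worsening of psychiatric symptoms, the patient’s participation will be stopped immediately". Exclusion criterion 1 lists severe states such as psychotic depression and imminent suicidal ideation. It does not list worsening as such.

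**Timing and analysis**
- Study procedure spaces assessments 4 months apart. T1–T2 is program time in the intervention group and waiting time in the control group.
- Major statistical analysis specifies intention-to-treat on all randomized subjects, with multiple imputation for missing data.

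**The concern.** The rules for taking a patient off study do not agree with one another, and the broader ones are written for the waiting group alone. A site could keep or remove the same waiting patient depending on which paragraph it follows. For at least one event, a literal reading removes a waiting patient while stating no medication trigger for a program patient.

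This matters because a need for psychotropic medication and psychiatric worsening are both tied to depression, the primary outcome. Removal would then be related to outcome and could differ by arm in the interval on which the randomized contrast depends. Once the waiting group starts BA after T2, there is no untreated comparator.

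If a removed waiting patient also received an equivalent program before T2, the control condition itself would be diluted.

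**Working it through.** No figure in the plan is in dispute, so the check is to run the same event through each passage and then ask what can be said about bias.

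**Event A: one temporary emergency psychotropic dose between T1 and T2, waiting patient**
- Exclusion criterion 3: excepted, so the patient stays.
- Discontinuation criterion 5: not regular use, so the patient stays.
- Discontinuation criterion 6: refers back to the exclusion criteria, where the exception applies, so the patient stays.
- Last paragraph of Exclusion criteria: a need for medication has arisen, so the patient leaves.

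**Event A, program patient**
- Exclusion criterion 3 and discontinuation criterion 5 give the same answer: stays.
- Criterion 6 and the last paragraph of Exclusion criteria do not apply to this patient.
- No stated medication trigger is met. Only the physician's general discretion (discontinuation criterion 7) remains.

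Three provisions thus keep the waiting patient and one removes them. The one that removes has no counterpart in the other arm.

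**Event B: psychiatric worsening short of the severe states in exclusion criterion 1**
- Discontinuation criterion 2: the bar is that the intervention cannot be continued.
- Closing paragraph of Discontinuation criteria: the bar is that continuing is judged difficult.
- Patient disadvantages: worsening is given as an example of meeting an exclusion criterion, although no exclusion criterion is worded that way.

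The text therefore gives two bars and one cross-reference to a criterion that is not listed. Both bars are phrased around continuing an intervention that a waiting patient has not begun.

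**Direction of bias if T2 is lost after removal**

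Let q be the fraction of an arm removed, and D the amount by which the T2 mean the removed patients would have had exceeds that of those kept. The full-arm mean is (1 − q) × kept mean + q × removed mean, so

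kept mean − full mean = −q × D.

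With benefit defined as waiting mean minus intervention mean, and W and I marking the two arms, the observed benefit is

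true benefit − (q_W × D_W − q_I × D_I).

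- If removed patients are more depressed, D is positive. If removal is more frequent in the waiting arm and D is similar in the two arms, the bracket is positive and the benefit is understated.
- If q and D are equal in the two arms, the bracket is zero.
- The expression describes the comparison without imputation. Multiple imputation could recover what the T1 score predicts. It could not reliably recover worsening after T1, because no BDI-II is scheduled between T1 and T2.

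**Why no size follows**

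Neither q nor D is given for either arm. The only attrition figure, in Power and sample calculation, is 3 of 32 (3/32 = 9.4%, taken as 10%). It comes from a pre-post study without a control group, hence without a waiting period. The dropout it allows for is defined to leave out patients who meet the exclusion criteria, so removals under discontinuation criterion 6 fall outside it.

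**The case against.** The strongest reply is that the operative medication rule, discontinuation criterion 5, is expressly symmetric. On this view the waiting-group sentence merely reports what patients are told, and a need for medication is shorthand for a need for regular pharmacotherapy. That reading is possible, but the text does not state it, and patients would be given the broader version. The mismatch stands.

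Several stronger readings are tempting, and the objection to them succeeds:

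- *Any worsening removes a waiting patient but not a program patient.* The sentence in Patient disadvantages is conditional on exclusion criteria being met. Worsening can be read as an example of how that happens, such as decline into one of the severe states in exclusion criterion 1. The next sentence, on patients with BDI-II of 21 or more, ends participation on worsening by reference to the discontinuation criteria and is not limited to one arm. The closing paragraph of Discontinuation criteria and criterion 7 also allow program patients to be stopped. An arm difference in the handling of worsening is not established; an inconsistency is.
- *The offers after removal contradict each other.* The equivalent program is tied to a need for medication, and psychiatric treatment to meeting the exclusion criteria. These are different events and the offers are compatible. The document gives no timing for the equivalent program, so receipt before T2 is a possibility only.
- *The bias can be sized from the T1-to-T2 rise in BDI-II.* No passage makes a BDI-II rise a trigger. Anyone whose rise has been measured at T2 already has the score that such a calculation treats as lost.
- *Removed patients leave the analysis.* Major statistical analysis covers all randomized subjects, and Study procedure keeps registrations in the database unless consent is withdrawn. The document does not say that removed patients are dropped.

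**Conclusion.** The concern holds as an inconsistency with a possible consequence for the comparison. The firm part is medication: the waiting-group sentence in Exclusion criteria conflicts with exclusion criterion 3 and discontinuation criterion 5, and it is easier to trigger than either. Discontinuation criterion 6 adds a second route written only for waiting patients. The worsening wording is inconsistent as well, but an arm difference there is not shown.

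A bias follows only if removal is more frequent in the waiting arm, if removed patients are more depressed than those kept, and if their T2 scores are lost and not recovered by imputation. Under those assumptions the direction is toward no effect. The error would hide a benefit of BA and would not create one. The magnitude cannot be derived from the document. The three-timing ANOVA does not single out T2 as primary; T2 matters because it ends the only interval with an untreated comparator.

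**What to change.** 1. Reconcile Exclusion criteria (item 3 and the last paragraph), Discontinuation criteria (items 2, 5 and 6 and the closing paragraph), Patient disadvantages, and what waiting patients are told, into one consistent statement of the medication trigger and the worsening trigger.
2. State whether that statement applies alike to both arms between T1 and T2. Which rule applies is for the investigators to decide.
3. In line with the stated intention-to-treat principle, say that removed patients remain in the analysis and that their T2 BDI-II will be sought. Where an equivalent program is given before T2, obtain the BDI-II before it starts.
4. Flag patients who receive an equivalent program before T2 as early crossovers.

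The cost is a wording amendment, one flag on the case form and an occasional early questionnaire. No additional patients are needed.
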